## Abstract

**Introduction:**

Previous novel COVID-19 pandemics, SARS and middle east respiratory syndrome observed an association of infection in pregnancy with preterm delivery, stillbirth and increased maternal mortality. COVID-19, caused by SARS-CoV-2 infection, is the largest pandemic in living memory.

Rapid accrual of robust case data on women in pregnancy and their babies affected by suspected COVID-19 or confirmed SARS-CoV-2 infection will inform clinical management and preventative strategies in the current pandemic and future outbreaks.

**Methods and analysis:**

The pregnancy and neonatal outcomes in COVID-19 (PAN-COVID) registry are an observational study collecting focused data on outcomes of pregnant mothers who have had suspected COVID-19 in pregnancy or confirmed SARS-CoV-2 infection and their neonates via a web-portal. Among the women recruited to the PAN-COVID registry, the study will evaluate the incidence of: (1) miscarriage and pregnancy loss, (2) fetal growth restriction and stillbirth, (3) preterm delivery, (4) vertical transmission (suspected or confirmed) and early onset neonatal SARS-CoV-2 infection.

Data will be centre based and collected on individual women and their babies. Verbal consent will be obtained, to reduce face-to-face contact in the pandemic while allowing identifiable data collection for linkage. Statistical analysis of the data will be carried out on a pseudonymised data set by the study statistician. Regular reports will be distributed to collaborators on the study research questions.

**Ethics and dissemination:**

This study has received research ethics approval in the UK. For international centres, evidence of appropriate local approval will be required to participate, prior to entry of data to the database. The reports will be published regularly. The outputs of the study will be regularly disseminated to participants and collaborators on the study website (https://pan-covid.org) and social media channels as well as dissemination to scientific meetings and journals.

**Study registration number:**

ISRCTN68026880.

Strengths and limitations of this studyThe pregnancy and neonatal outcomes in COVID-19 (PAN-COVID) registry aims to collect an international data set, which will enable us to answer a focused set of questions related to pregnancy, maternal and neonatal outcomes of SARS-CoV-2 infection in pregnancy.There is a high likelihood of an adequate sample size to allow us to measure all the stated focused outcomes of SARS-CoV-2 infection in pregnancy.The PAN-COVID protocol facilitates data sharing and collaboration with multiple global partners.This registry establishes a collaborative framework, which can be used to respond effectively to guide care for women in pregnancy and their neonates in future pandemics.Registry studies are generally unlikely to fully capture all cases and therefore carry risk of underestimating infection rates and overestimating infection complication and fatality rates.

## Introduction

The majority of all new, emerging or re-emerging viruses affecting the human population in the recent years are zoonoses, including HIV/AIDS, SARS, the H5N1 strain of avian influenza, the 2009 pandemic H1N1 influenza virus, the middle east respiratory syndrome (MERS), the Zika and Nipa viruses^1 2^ and most recently COVID-19 caused by SARS-CoV-2 virus. The spread of these infections in an immune-naïve human population, as shown by the recent COVID-19 pandemic poses serious strain on public health. To tackle such large pandemics, international collaborative and multidisciplinary approaches are necessary.

These should aim to identify those at highest risk of exposure to emerging pathogens, to characterise the culture and practices that modify their risk (eg, the presence of live animal markets and the use of face masks in South-East Asia) and to develop preventative interventions accordingly.^3 4^ Pregnant women infected with SARS or MERS were at increased risk of mortality and morbidities such as stillbirth, preterm birth and fetal growth restriction (FGR).^5 6^ Case series for pregnant women infected during outbreaks of SARS^7^ or MERS^8^ report a variety of different outcomes, with variable recording of diagnostic testing, maternal, fetal and neonatal outcomes and the presence or absence of vertical transmission. Clinical outcomes appear worse for pregnant compared with non-pregnant women infected with SARS and H1N1 influenza.^7 9^

As of the 12 May 2020, after disambiguation and removal of duplicate reporting, the rolling review of all cases worldwide conducted by Thornton et al^10^ contains 92 publications including details of 806 pregnant women and 674 fetuses. At the time of writing this protocol, 457 of the included women had delivered and were alive and 21 women had died. These women had delivered 428 babies, of which 94 were born preterm, 17 were infected with COVID-19, and there were 15 neonatal deaths. The largest study to date has been from the UK (Knight et al) who reported 427 cases (247 completed pregnancies): there were five (1%) maternal deaths, three (1%) stillbirths and two (1%) neonatal deaths.^11^ There are currently limited data on the effect of COVID-19 on second trimester miscarriage^12^ and no available data on first trimester miscarriage or growth restriction. The risk of reported probable vertical transmission of SARS-CoV-2 infection is estimated at 2.5% in women admitted to hospital with COVID-19; with case reports describing increased SARS-CoV-2 IgM levels in neonates, and pneumonia and lymphopaenia in neonates with negative COVID-19 reverse transcription-PCR testing, principally from nasopharyngeal swabs.^13 14^

There are major knowledge gaps on the effect of COVID-19 on various stages of pregnancy, and its effect on fetuses in terms of growth restriction, prematurity and short and long term morbidities.^15^ There is an urgent need to collect case data rapidly, to pool global data on the natural history of women affected by suspected COVID-19 or confirmed SARS-CoV-2 in pregnancy to inform treatment and implement preventative strategies in the current and future outbreaks. Published case series are almost always out of date when published and cases may overlap. A centre-based registry, gathering case data prospectively on the effect of SARS-CoV-2 infection from healthcare systems around the world offers a method to accrue clinical outcomes on key research questions from a variety of populations and healthcare systems without these limitations.

The pregnancy and neonatal outcomes of COVID-19 (PAN-COVID) registry will focus on miscarriage, FGR, stillbirth, preterm delivery and vertical transmission (suspected or confirmed) and early onset neonatal SARS-CoV-2 infection and will include fields on ultrasound diagnosis and neonatal care not included in other more general studies. This study will identify cases that should also be reported to International Network of Obstetric Survey Systems (INOSS) population-based surveillance systems of confirmed COVID-19 cases admitted to hospital through existing reporting mechanisms. The UK’s obstetric surveillance system (UKOSS) is a population surveillance study, reporting women in pregnancy hospitalised with COVID-19 or SARS-CoV-2 infection. The PAN-COVID registry is distinct in that it will collect, via a web portal, data on SARS-CoV-2 infections in pregnancy, whether the diagnosis is presumptive based on symptoms or following a positive test and whether the patient is admitted to hospital or not. Given that the SARS-CoV-2 virus is likely to affect a high proportion of the global population and adverse outcomes may influence policy and practice in a short time frame, ‘real-time’ high-level reporting on a regular basis will be valuable for UK and international clinicians and policymakers.

PAN-COVID registry will work collaboratively with approved studies and registries to ensure that the global impact of the pandemic is captured as fully as possible, with data sharing and linkage. PAN-COVID has established links with the UK National Neonatal Research Database (NNRD) (REC Reference: 16/LO/1093) who will provide data on neonatal outcomes, and the British Paediatric Surveillance Unit with whom there is in principle an agreement for data sharing. In the UK, the PAN-COVID registry will signpost to UKOSS where the case definition requires a more detailed data collection. We are in discussions with international studies including the American Academy of Pediatrics (AAP) Section of Neonatal Perinatal Medicine (SONPM) to agree on a common data set to enable future merging of information.

## Methods and analysis

This is an observational global pregnancy and neonatal register (PAN-COVID registry) collecting outcome data from women in pregnancy who have confirmed SARS-CoV-2 infection or signs and symptoms of COVID-19 during their pregnancy. The study is sponsored by Imperial College London and funded by UK Research Institute and National Institute of Health and Research (NIHR). The study received Urgent Public Health (UPH) prioritisation in the UK in April 2020.

The main study objectives are, first, to establish a UK and international disease registry for women with suspected COVID-19 or confirmed SARS-CoV-2 infection in pregnancy; in the UK, this will be linked to neonatal data (from NNRD). Second, PAN-COVID investigators aim to publish regular reports focused on our principle research question: in women recruited to the PAN-COVID registry with suspected or confirmed SARS-CoV-2 infection, what is the incidence of (a) miscarriage, (b) small for gestational age (SGA)/FGR and stillbirth, (c) preterm birth and (d) suspected or confirmed vertical transmission to the neonate and perinatal infection.

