### Data entry

Demographics—date of birth, National Health Service (NHS) number (or international equivalent), smoking status, last menstrual period, expected date of delivery, body mass index, history of previous pregnancies/miscarriages/loss/small for gestational age/delivery (preterm/term), comorbidities, medications, ethnicity, number of fetuses, structural abnormality on ultrasound.

COVID-19 signs and symptoms—fever, new persistent cough, anosmia, myalgia, diarrhoea, shortness of breath, fatigue, abdominal pain, chest pain, hoarseness of voice, loss of appetite, delirium.

SARS-CoV-2 infection—SARS-CoV 2 test performed, date of test(s), results of test(s) (if available)

COVID-19 treatment—requirement for (including duration of) inpatient, level 2 or 3 critical care, supplementary oxygen, non-invasive ventilation, endotracheal intubation, extracorporeal membrane oxygenation, antiviral/other specific anti-COVID-19 therapy, iatrogenic delivery or termination due to maternal compromised from COVID-19.

Maternal outcomes—non-invasive ventilation, intubation and ventilation and maternal death.

Comorbidities—hypertension, respiratory disease, cardiovascular disease, renal disease, autoimmune disease, medications including aspirin, progesterone, others.

Delivery details—iatrogenic/spontaneous, date of delivery/miscarriage, mode of delivery, live birth/stillbirth/miscarriage, birth weight, sex.

Postnatal outcomes—breastfeeding, baby cared for separately from mother until discharge.

Neonatal outcomes—date of birth, birth weight, gestation at birth, Apgar at 5 min, neonatal death, COVID-19 transmission (neonate with positive swab/serology), congenital abnormality/deformation, date of discharge from hospital, readmission up to 28 days of life.

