### Study population

Study centres will be asked to identify eligible women of childbearing age (18–50 years) at the time of an early pregnancy attendance or at delivery who have had suspected COVID-19 or confirmed SARS-CoV-2 infection in pregnancy. Case data will be entered into the online registry. The study will recruit women affected by suspected COVID-19 or confirmed SARS-CoV-2 infection from January 2020 and March 2021. Participants will be able to withdraw from the register at any time without affecting their medical care. Participants should inform any member of the study team of their wish to withdraw consent. When a participant withdraws consent, they should be asked whether they are willing to allow ongoing data collection, such as maternal and fetal outcomes, from their medical records. If the participant withdraws consent and does not wish to have any further data collected, then this will be recorded on the database and no further data entry will be possible.

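### Untested women can enter on symptoms that overlap with miscarriage, and the final analysis as described does not separate them, so the loss itself can raise the miscarriage estimate

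*Protocol article*

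**What the plan says.** The Methods and analysis section of the protocol article defines the population as pregnant women "who have confirmed SARS-CoV-2 infection or signs and symptoms of COVID-19 during their pregnancy". The Introduction confirms that no test is needed: cases are collected "whether the diagnosis is presumptive based on symptoms or following a positive test", in or out of hospital.

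Under Study population, centres identify women "at the time of an early pregnancy attendance or at delivery who have had suspected COVID-19 or confirmed SARS-CoV-2 infection in pregnancy".

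Under Data entry, the fields headed as COVID-19 signs and symptoms start with fever, new persistent cough and anosmia, and end with "fatigue, abdominal pain, chest pain, hoarseness of voice, loss of appetite, delirium". The article has no other list of COVID-19 symptoms. No number, combination or timing of symptoms is attached to it, and it is not called a case definition. The date of delivery or miscarriage is a listed field. Test dates are listed, but a symptom onset date is not.

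The principal question in Methods and analysis pools suspected and confirmed women, and miscarriage is its first outcome. The reporting plan, at the end of the Sample size section, has three levels:

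- **Bulletins** give the distribution of diagnosis status (suspected, positive, negative) and, separately, the outcome of delivery including miscarriage. No cross-tabulation of the two is stated.
- **The interim analysis** splits its outcomes by suspected and confirmed diagnosis. They are gestation at delivery, birth weight Z-scores, perinatal mortality, neonatal swab positivity, neonatal morbidity and maternal death. Miscarriage is not named.
- **The final analysis** covers baseline data for the whole cohort and all outcomes, with confidence intervals by country where numbers allow. No split by diagnosis status is stated.

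**The concern.** For most outcomes, counting an uninfected woman as a suspected case only dilutes the estimate: she carries roughly the background risk and pulls the result towards it. Miscarriage is different. Abdominal pain can be a symptom of the loss, and an early pregnancy attendance is where a loss may be found. If the pain contributes to a suspected diagnosis made at that attendance, the outcome has helped to supply the exposure, and the miscarriage proportion rises without any effect of infection.

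The stakes are highest for miscarriage because the Introduction says that no first trimester data exist and that adverse outcomes may influence policy and practice quickly. The Sample size section also plans to set results against background rates from other registries, so misclassification would pass straight into that comparison.

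The point concerns untested women. Women with a positive test are not affected, and women with a negative test can be identified from the recorded results.

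**Working it through.** **The plan's own figures.** The Sample size section gives background rates of 30% (miscarriage), 10% (SGA/FGR) and 0.2% (stillbirth), and expected pandemic rates of 40%, 15% and 0.4%. Its only calculation is the 95% CI half-width at n = 500, stated as 4.2, 2.9 and 0.3 points. The usual formula, 1.96 × √(p(1−p)/500), gives 4.29, 3.13 and 0.55. That mismatch is a separate matter and nothing below depends on it.

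The article does not say what share of suspected women are truly infected, or what share enter only on non-specific symptoms. Both are assumed here and shown over a range.

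**Upward error, miscarriage.** Let s be the share of suspected women at early pregnancy attendance who entered only on non-specific symptoms, and m their loss rate. With no true effect of infection, the observed rate is (1 − s) × 30% + s × m.

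| s | m = 50% | m = 70% |
|---|---|---|
| 5% | 0.95×30 + 0.05×50 = 31% | 0.95×30 + 0.05×70 = 32% |
| 10% | 0.90×30 + 0.10×50 = 32% | 0.90×30 + 0.10×70 = 34% |
| 20% | 0.80×30 + 0.20×50 = 34% | 0.80×30 + 0.20×70 = 38% |

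The protocol expects a rise of 10 points (30% to 40%). At m = 50%, the error is 1, 2 or 4 of those points. These figures apply only to suspected women identified at early pregnancy attendance. In the whole cohort the error shrinks in proportion to that group's share, which is not given.

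**Downward error, other outcomes.** Let v be the share of suspected women truly infected, with the rest at background risk. The observed rate is v × expected + (1 − v) × background.

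| v | SGA/FGR (15% if all infected) | Stillbirth (0.4% if all infected) |
|---|---|---|
| 0.75 | 0.75×15 + 0.25×10 = 13.75% | 0.75×0.4 + 0.25×0.2 = 0.35% |
| 0.50 | 0.50×15 + 0.50×10 = 12.5% | 0.50×0.4 + 0.50×0.2 = 0.30% |

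For SGA/FGR, a quarter to a half of the expected 5-point excess is lost. Dilution exceeds the stated half-width of 2.9 points only when v falls below 1 − 2.9/5 = 0.42.

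**Can the stated reporting reveal either error?** For the outcomes on the interim list, partly, because suspected and confirmed women are shown apart. For miscarriage, no: it is not on that list, the bulletins do not cross it with diagnosis status, and no split is stated for the final analysis.

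**The case against.** The strongest reply is that the symptom list is not an entry rule. It sits under Data entry with smoking status and Apgar score, as information recorded on registered women. Entry requires a suspected or presumptive diagnosis, and no section says that one ticked symptom suffices. This stands. A reader might infer that abdominal pain alone qualifies a woman, but the article does not say so.

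The article also condenses a full protocol, which may hold an operational definition of suspected COVID-19. That stands too, so the lack of a detailed definition is not the point made here. The point rests on what the article does state: symptom-based entry, case-finding at early pregnancy attendance, a pooled principal question, and a reporting plan that does not separate miscarriage by diagnosis.

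Including untested women is deliberate: the Introduction contrasts the registry with surveillance of hospitalised women. Some loss of specificity is the price, and this write-up does not ask for their exclusion.

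The order of onset and loss may already be derivable. The Sample size section plans an interval from onset of suspected or confirmed COVID-19, which needs an onset date, and the miscarriage date is recorded. This is correct and makes the remedy cheap, but the stated analysis does not use that order to decide who counts.

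Two further inferences are tempting because recruitment covers "women affected by suspected COVID-19 or confirmed SARS-CoV-2 infection from January 2020 and March 2021": that winter respiratory infections were counted as COVID-19, and that women with poor outcomes recall symptoms more readily. Both are plausible, but the article says nothing about other infections, test availability at the time or exposure taken from recall.

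**Conclusion.** The concern holds in a limited form. Under the plan as described, symptoms of a miscarriage can contribute to a woman being counted as suspected COVID-19, and the stated reporting would not show how far this raises the miscarriage estimate. Other outcomes can be pulled towards background by uninfected women.

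The size is unknown. The illustrations give 31% to 34% against a 30% background for suspected women at early pregnancy attendance (s of 5% to 20%, m = 50%), and SGA/FGR of 13.75% to 12.5% against 15% (v of 0.75 to 0.50). They rest on assumed shares, an assumed loss rate, and the protocol's 30% serving as background for women at such attendances.

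A reader might conclude that the whole-cohort results cannot be interpreted. That does not follow: confirmed women are unaffected, the size of the affected group is not given, and the interim split helps for the outcomes it lists. The supported conclusion is that the miscarriage result in untested women needs a timing condition and separate reporting before it is set against background rates.

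**What to change.** 1. In the final analysis, report every outcome, including miscarriage, separately for test-positive, suspected untested and test-negative women. The bulletins already use these three categories.
2. For the miscarriage estimate, count a suspected untested woman only if symptom onset precedes the attendance at which the loss was diagnosed. Use the onset date that the infection-delivery interval already needs, with the recorded miscarriage date.
3. Show untested women without fever, new persistent cough or anosmia in a separate 'possible' row. This is needed as well as step 2, because pain from a loss can begin before the attendance.
4. Use the restriction to those three symptoms as a sensitivity analysis, not as the primary definition. The article does not give it as a case definition, and it could drop true cases with, for example, shortness of breath or myalgia.

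If the full protocol or the analysis plan already contains a case definition or an ordering rule, state it in the final report and apply steps 1 and 3.

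**Cost.** The symptom fields, test results and miscarriage date are already collected, so most of this is derived variables and extra table rows. It must be confirmed that the form captures an onset date, since Data entry lists only test dates for the infection. The price is a smaller suspected group in the miscarriage estimate and wider intervals within strata. Nobody is removed from the registry.

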### Data entry

Demographics—date of birth, National Health Service (NHS) number (or international equivalent), smoking status, last menstrual period, expected date of delivery, body mass index, history of previous pregnancies/miscarriages/loss/small for gestational age/delivery (preterm/term), comorbidities, medications, ethnicity, number of fetuses, structural abnormality on ultrasound.

COVID-19 signs and symptoms—fever, new persistent cough, anosmia, myalgia, diarrhoea, shortness of breath, fatigue, abdominal pain, chest pain, hoarseness of voice, loss of appetite, delirium.

SARS-CoV-2 infection—SARS-CoV 2 test performed, date of test(s), results of test(s) (if available)

COVID-19 treatment—requirement for (including duration of) inpatient, level 2 or 3 critical care, supplementary oxygen, non-invasive ventilation, endotracheal intubation, extracorporeal membrane oxygenation, antiviral/other specific anti-COVID-19 therapy, iatrogenic delivery or termination due to maternal compromised from COVID-19.

Maternal outcomes—non-invasive ventilation, intubation and ventilation and maternal death.

Comorbidities—hypertension, respiratory disease, cardiovascular disease, renal disease, autoimmune disease, medications including aspirin, progesterone, others.

Delivery details—iatrogenic/spontaneous, date of delivery/miscarriage, mode of delivery, live birth/stillbirth/miscarriage, birth weight, sex.

Postnatal outcomes—breastfeeding, baby cared for separately from mother until discharge.

Neonatal outcomes—date of birth, birth weight, gestation at birth, Apgar at 5 min, neonatal death, COVID-19 transmission (neonate with positive swab/serology), congenital abnormality/deformation, date of discharge from hospital, readmission up to 28 days of life.

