### Sample size

Prespecified sample size estimation was not carried out given the aim of this observational study was to collate all consecutive eligible case outcomes in participating centres between data collection start and 18 months from start of data collection. It may be useful to provide an approximate guide as to the width of the 95% CI that can be achieved for proportions using historical data from the UK. These historical data may not hold during the current pandemic and may alter due to multiple reasons such as access to healthcare or behaviour changes. Contemporaneous data collected using other current national registries will provide true background rates for comparative purposes at the end of the study period. Generalising these data internationally may not be possible unless similar contemporaneous data exist for comparison.

The estimated representative pre-COVID pandemic incidences of miscarriage, Small for Gestational Age (SGA)/FGR and stillbirth in the UK were 30%, 10%, 0.2%, respectively. The expected outcome proportions during the COVID-19 pandemic are 40%, 15% and 0.4%, respectively. A sample size of 500 would allow the estimation of the width of 95% CIs for the proportion of miscarriage as 40%±4.2%, for SGA/FGR 15%±2.9% and for stillbirth 0.4%±0.3%.

These figures are meant only as a guide and reference proportions may change over this period. Since attaining sufficient precision for stillbirth requires by far the largest sample size, then study recruitment targets could be based on this rarest of outcomes. This would then provide sufficient precision to assess other more common outcomes. These figures are based on data from the UK only. Reference proportions vary by country but are of a similar order to those in the UK.

Appropriate quantitative analyses will be conducted by a study statistician. Dates collected from sites for expected data of delivery or last menstrual period, week of pregnancy at delivery and date of any COVID-19 tests in the participant or neonate will be cross-checked and validated for the final report. Regular interim reports will use contemporaneous data as it is collated.

Derived variables to be reported are:

Infection delivery interval (<2 or≥2 weeks after onset of suspected or confirmed COVID-19).Week of pregnancy when COVID-19 diagnosis was made.Number of days from delivery to SARS-COV-2 testBirth weight percentiles adjusted for gender and gestational age.

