Fortnightly bulletins will consist of counts of participants by country, proportions for maternal COVID-19 diagnosis status (suspected, positive test, negative test), week of pregnancy for COVID-19 diagnosis (<23 weeks, 23–36 weeks, ≥37 weeks), weeks of pregnancy at delivery (<23 weeks, 23–36 weeks, ≥37 weeks), maternal and neonatal mortality, outcome of delivery (live birth, miscarriage, intrauterine death, stillbirth (>22+6 weeks gestation)), FGR split by delivery interval (<2 vs ≥2 weeks), COVID-19 diagnosis status for babies split by number of days from delivery to test (0, 1–7, 8–28) and birth weight percentiles. Mean (SD) and median birth weights will also be reported. Further analysis will take place at one interim time point and at final data collection. For the interim analysis, a subset of validated outcomes will be reported consisting of total cohort proportions of gestation at delivery, birth weight Z-scores, perinatal mortality (stillbirth, early neonatal death), neonatal COVID-19 or SARS-COV-2 swab positive, neonatal morbidity and maternal death. These data will be split by suspected and confirmed COVID-19 diagnosis. Additional graphical exploratory analysis of the data will assess any possible association between the infection delivery interval and the timing of delivery as well as birth weight. The final analysis will report all demographic baseline data for the whole cohort and all outcomes as well as these graphical trends. Proportional data for the study outcomes will be presented with 95% CIs, by country, where numbers allow. Data and all appropriate documentation will be stored for a minimum of 10 years after the completion of the study, including the follow-up period.

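### Neonatal transmission is recorded from any positive swab or serology, and neither antibody class, age at test nor a tested-baby denominator is tied to the vertical transmission outcome

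*Protocol article*

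**What the plan says.** All references are to the protocol article.

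- **The outcome.** The Abstract (Methods and analysis) lists "vertical transmission (suspected or confirmed) and early onset neonatal SARS-CoV-2 infection" among four groups of outcomes. The main Methods and analysis section puts "suspected or confirmed vertical transmission to the neonate and perinatal infection" into the principal research question. Neither place says what separates a suspected from a confirmed case.
- **The recorded item.** Under Data entry, the neonatal item is "COVID-19 transmission (neonate with positive swab/serology". It names no antibody class and no age at sampling.
- **Timing.** The analysis text under Sample size includes days from delivery to test among the derived variables, and says that the "date of any COVID-19 tests in the participant or neonate will be cross-checked and validated for the final report". The bulletins will show "COVID-19 diagnosis status for babies split by number of days from delivery to test (0, 1–7, 8–28" days.
- **Interim analysis.** The same section says that "a subset of validated outcomes will be reported consisting of total cohort proportions of gestation at delivery", and the list continues to "neonatal COVID-19 or SARS-COV-2 swab positive, neonatal morbidity and maternal death". The next sentence splits these data by suspected and confirmed COVID-19 diagnosis.
- **Final analysis.** All outcomes are reported, with 95% confidence intervals by country where numbers permit. No denominator of tested babies is named.

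**The concern.** The data item turns a test result into a conclusion about route. IgG in a newborn can be the mother's own antibody, and the registry takes women infected at any point in pregnancy, so some mothers may well have antibody by the time of birth. The Introduction itself cites raised neonatal IgM, not serology in general, as the relevant report. A first positive at 8–28 days may be postnatal infection. The information needed to set such babies apart by timing is collected, but it is not used to define the outcome.

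The denominator matters separately. The Outcomes section takes outcomes from routine medical records, so who is tested depends on local practice. If babies never tested are included in the denominator, differences between countries or centres will partly be differences in testing policy.

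At stake is one of the registry's four headline incidences, in a study that expects its reports to influence policy quickly.

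**Working it through.** The article gives no sample size, precision or expected rate for vertical transmission, so there is no figure of the plan's own to reproduce. The check is a comparison of the passages, followed by an illustration.

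**Comparison.** The outcome has four descriptions: vertical transmission with early-onset infection (Abstract), vertical transmission with perinatal infection (Methods and analysis), any positive swab or serology (Data entry), and neonatal COVID-19 or a positive swab (interim analysis). These need not select the same babies. The interim item names swab but not serology, and whether neonatal COVID-19 includes a serological diagnosis is not stated. The day bands appear only in the bulletin sentence. The derived days-to-test variable is to be reported, but no passage uses it to classify a case.

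**Inputs from the article (Introduction).**
- Probable vertical transmission of 2.5%, in women admitted to hospital.
- 17 infected among 428 babies in a rolling review: 17/428 = 3.97%.

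**Inputs assumed, because the article gives none.**
- Fraction of babies tested, f: 25% to 100%.
- Share of tested babies with serology, s: 5% to 20%.
- Share of those carrying passive maternal antibody, a: 30% to 90%.

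**Denominator.** With rate p among tested babies, and untested babies included as not positive, the total-cohort proportion is p × f.

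| f | p = 2.5% | p = 3.97% |
|---|---|---|
| 25% | 0.6% | 0.99% |
| 50% | 1.25% | 1.99% |
| 75% | 1.9% | 2.98% |
| 100% | 2.5% | 3.97% |

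**Case rule.** If every true case tests positive and passive antibody is independent of true infection, the apparent rate among tested babies is p + (1 − p) × s × a. With p = 2.5%:
- s = 5%, a = 30%: 0.025 + 0.975 × 0.05 × 0.30 = 3.96%
- s = 10%, a = 60%: 0.025 + 0.975 × 0.10 × 0.60 = 8.35%
- s = 20%, a = 90%: 0.025 + 0.975 × 0.20 × 0.90 = 20.05%

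**Both together.** This applies only if serology also enters the total-cohort item, which the article does not say. With s = 10% and a = 60%, the figure is 8.35% × 0.25 = 2.09% when a quarter are tested and 8.35% × 0.50 = 4.2% when half are. It crosses the true 2.5% at f = 2.5/8.35 = 30%. The two errors therefore oppose each other, and the net direction depends on inputs that are not known.

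**The case against.** The strongest reply is that Data entry is a condensed list of domains in a journal article, not the case report form. Antibody class, specimen type and case criteria may be set out in the full protocol, the form or an analysis plan that is not shown. That is fair, and it means nobody can say from this article that the form fails to record them. It does not remove the point, because the article goes beyond omitting detail: it equates a positive swab or serology with transmission.

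A reader might infer that the plan reports any positive swab or serology over the whole cohort. The documents do not support that. The swab/serology wording belongs to the data item, while the item under total-cohort proportions names swab only. Passive antibody reaches that proportion only if neonatal COVID-19 is taken to include serology.

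A reader might also infer that untested babies are counted as negative. That is not stated. Total cohort may mean pooled, as against the suspected/confirmed split in the next sentence. The phrase is used for the interim analysis only, and the bulletin table by days to test can be built only from tested babies.

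Timing is partly handled: days to test is derived and reported, and test dates are validated for the final report. The outcome is also worded to include perinatal or early-onset infection, so not every postnatal positive falls outside it. What remains is that the bands are not linked to a definition of vertical transmission.

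Using the infection-delivery interval for fetal growth restriction but not for neonatal infection is not an error. Such a split would be an optional extra analysis.

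**Conclusion.** The point holds in limited form. As written, the case rule can count passive maternal IgG and later postnatal infection as transmission. Suspected and confirmed cases are not distinguished. The day bands are not carried into the outcome at the interim or final analysis, and no tested-baby denominator is stated.

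The size cannot be fixed from the article. If untested babies are included, 2.5% among tested becomes 1.25% with half tested, and 0.6% to 1.9% with 25% to 75% tested. Unrestricted serology could make a true 2.5% appear as about 4% to 20% among tested babies under the assumed ranges. The 2.5% itself comes from women admitted to hospital, whereas the registry also takes women who were not, so it serves only as a scale.

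The material does not show a net bias in either direction, nor that the result would be uninterpretable. It does show a definition and a denominator that should be settled before the interim analysis.

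**What to change.** 1. Record swab, IgM and IgG as separate results, each with its test date. If the form already does this, say so in the protocol.
2. Do not count IgG alone as transmission.
3. Prespecify confirmed, suspected and indeterminate/postnatal categories. They should cover all three existing bands (day 0, days 1–7, days 8–28) so that first positives in the middle band are also classified. The criteria themselves are for the sponsor and its neonatal advisers to set.
4. Use these categories in the interim and final analyses as well as in the bulletins, and state whether neonatal COVID-19 in the interim list includes serology.
5. Report the numbers of babies tested and not tested, by country where the outcome is shown by country. Make tested babies the primary denominator and give the total-cohort figure as secondary only.

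**Cost.** At most one data field is split and the analysis text changes; test dates are already planned for collection and validation. Antibody class may be hard to recover later if it is not captured at entry, so the change is best made early. Some babies will move to an indeterminate class. The tested-only rate will reflect who was selected for testing, which is why the number not tested must be shown beside it.
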